### 3. STUDY DESIGN

A pragmatic multicentre non-inferiority randomised controlled trial of ESWL as first treatment option compared with direct progression to ureteroscopic treatment for ureteric stones (incorporating an internal feasibility phase). A summary of the trial design is shown in Figure 1.

#### 3.1. Intervention to be evaluated

- Extracorporeal shockwave lithotripsy (ESWL)
- Ureteroscopy

Extracorporeal shockwave lithotripsy (ESWL) involves generation of a shock-wave, external to the body, focused on the stone, causing it to fragment with the fragments subsequently passing spontaneously. A variety of systems (differing means of generating shock-waves, different focusing mechanisms) are available. It is routinely performed in an outpatient setting with pain relief or sedation as required. Recruitment will occur only in established centres with fixed-site lithotripters. This will allow some standardisation of protocols on times to treatment and ESWL delivery. Up to two sessions of ESWL will be considered as one intervention as per standard practice.

Ureteroscopy is the use of small semi-rigid or flexible ureteroscopes, in conjunction with intracorporeal lithotripsy devices, such as the holmium laser, to directly visualise and fragment ureteric stones. Smaller stones, in the lower ureter, can often be removed intact using basketing

devices. It is currently most often performed as a day-case procedure (but may require hospital admission depending on complexity) and usually requires general anaesthesia.

All post allocated treatment, auxiliary or additional procedures and interventions will be used as and when clinically indicated based on EAU/AUA and standard care guidelines. The reasons why further intervention may be required are similar across both arms. The decision about which further treatments are given will be influenced by the treatments that participants have already received and the need to treat any complications that may arise

Further interventions may include:

1. Extracorporeal shockwave lithotripsy (ESWL);
2. Urgent/elective ureteroscopy with stone fragmentation
3. Endoscopic insertion (or removal) of a stent in the ureter;
4. Percutaneous insertion of nephrostomy
5. Antegrade insertion of a ureteric stent through a nephrostomy

**Figure 1 Flow Diagram: Randomised controlled trial comparing extracorporeal shockwave lithotripsy (ESWL) with ureteroscopic retrieval as first treatment options for urinary stones.**

[figure not shown]

## **3.2 Study population**

Adults ( $\geq 16$  years old), presenting with a unilateral ureteric stone within any segment of the ureter, confirmed by computed tomography scan of the kidneys, ureters, and bladder (CTKUB), who are judged clinically to require active intervention and are able to undergo either treatment, capable of giving written informed consent, which includes adherence with the requirements of the trial

### **3.2.1 Selection of participants**

As standard practice, clinicians will assess patients presenting with a suspected ureteric stone. A log will be taken of all patients assessed in order to document the reasons for non-inclusion in the study (e.g. reason they were ineligible, or declined to participate) to inform the CONSORT diagram.

Brief details of potentially eligible patients will be recorded in the screening logs at each site (these will be an aid to monitoring potential participant inclusion).

### **3.2.2 Planned inclusion and exclusion criteria**

#### **Inclusion criteria**

- Presence of stone confirmed by CTKUB
- Patients with a ureteric stone requiring removal
- Adults  $\geq 16$  years of age
- Single ureteric stone requiring treatment
- Suitable for either ESWL or ureteroscopic treatment
- Capable of giving written informed consent, which includes adherence with the requirements of the trial.

#### **Exclusion criteria**

- Pregnancy
- Stones not confirmed by CTKUB
- Bilateral ureteric stone(s)
- Patients with abnormal urinary tract anatomy (such as a horseshoe kidney or ileal conduit)
- Patients unable to understand or complete trial documentation

## **3.3 Recruitment and Study Procedures**

### **3.3.1 Identifying participants**

Local procedures at the participating hospitals are different and the timing and mode of approach to patients and the consent process will vary to accommodate both the variability at the sites and the needs of the patients. Following adequate pain relief and confirmation of ureteric calculi by CTKUB, eligible patients (according to the inclusion and exclusion criteria given in sections 3.2.2) will be provided with a patient information leaflet (PIL).

Each patient will have the opportunity to discuss the study with the local clinical team. Patients may make a decision to participate, during a consultation with the local clinical team during a visit to hospital (e.g. when they attend a clinic appointment or whilst a patient in hospital for their initial stone episode) or alternatively at home. If the patient agrees to be contacted at home he/she may receive a telephone call from the local Research Nurse to discuss any queries. Patients who decide to participate following telephone counselling can either send their completed documents (consent form and baseline questionnaire) through the post to the local team at their treating hospital or bring it with them if they are returning to hospital for another consultation or treatment. Participants will be

randomised to one of the two treatment groups following consent, completion and receipt of baseline questionnaire.

### **3.3.2 Informed consent**

The PIL explains that the trial is investigating the use of either ESWL or ureteroscopic treatment as the first treatment option for symptomatic ureteric stones that require an active intervention. Signed informed consent forms will be obtained from the participants in all centres. Participants who cannot give informed consent (e.g. due to incapacity) will not be eligible for participation. The participant's permission will be sought to inform their general practitioner that they are taking part in this trial.

### **3.3.3 Randomisation and allocation**

Eligible and consenting participants will be randomised to one of the two intervention groups using the telephone Interactive Voice Response (IVR) randomisation application or via the web based application - both hosted by the fully registered with the UK Clinical Research Collaboration (UKCRC), Clinical Trials Unit (CTU) at the Centre for Healthcare Randomised Trials (CHaRT), Health Services Research Unit (HSRU) in Aberdeen.

Randomisation will be minimised by centre, stone size ( $\leq 10\text{mm}$  or  $> 10\text{mm}$ , as measured by the maximum stone diameter on CT KUB) and location of the stone in either the upper, mid or lower ureter (as defined in the EAU/AUA Guidelines).

### **3.3.4 Follow-up procedures**

Eligible patients that have given signed informed consent to participate in the study will be asked to complete the EQ-5D, SF-12, pain score (NRS), use of analgesics at baseline and will then be randomised to either ESWL or ureteroscopic retrieval. Participants will be asked to complete the pain score, EQ5D, and use of analgesics questions (self completed) at their allocated intervention visit to secondary care immediately prior to receiving their interventions. At one week post intervention they will be asked to complete the pain score and use of analgesics questions by self completed questionnaire. Participants allocated to ESWL (up to two sessions of ESWL) will receive these questionnaires for their first session of ESWL. At eight weeks and then six months post randomisation participants will be asked to complete a questionnaire to measure the EQ-5D, SF-12, pain score (NRS), use of analgesics, complications, additional interventions received, and acceptability of the received procedure. In addition, at six months post randomisation, participants will be asked to complete questions relating to their primary and secondary care. Questionnaires and up to two reminders will be sent to participants by post, email or phone, taking into account any preferences they may have for mode of communication.. The case report forms (CRFs) at eight weeks and six months post randomisation will be completed and entered at site by the centre coordinators at the recruiting centres. They will collect additional interventions received and reasons for those, reasons why they might not have received their allocated intervention, complications and date of stone passage.

### **3.3.5 Withdrawal procedures**

Participants will remain on the trial unless they chose to withdraw consent or if they are unable to continue for a clinical reason. If a participant withdraws consent, participant questionnaires will not be collected, however permission will be sought for the research team to continue to collect outcome data from their health care records (via the CRFs). All other changes in of status with the exception of formal withdrawal of consent will mean the participant is still followed up for all study outcomes wherever possible.

### 3.3.6 Subsequent arrangements

#### Informing key people

Following formal trial entry:

The Study Office will:

- i) Inform the participant's General Practitioner (by letter enclosing information about TISU and Study Office contact details).

The local Research Nurse will:

- i) File the Hospital Copy of the Consent form in the hospital notes along with information about TISU.
- ii) Use the TISU internet database to enter data regarding the participant, including data required to complete randomisation
- iii) Return all study documentation to the Study Office in Aberdeen after database entry of essential data.

#### Notification by GPs

GPs are asked to contact the Study Office if one of the participants moves, becomes too ill to continue or dies, or any other notifiable event or possible serious adverse event occurs. Alternatively, staff at the Study Office may contact the GP.

## 4 SAFETY

The TISU trial involves procedures for treating ureteric stone which are well established in clinical practice. Adverse effects may occur during or after any type of surgery.

### 4.1 Definitions

An adverse event (AE) is defined as any untoward medical occurrence in a participant, not necessarily having a causal relationship.

Adverse events are not:

- continuous and persistent disease or symptom, present before the trial, which fails to progress;
- signs or symptoms of the disease being studied (in this case ureteric stones); or
- treatment failure.

An adverse event is defined as "serious" (SAE) if it

- Results in death
- Is life threatening
- Requires or prolongs inpatient hospitalisation
- Results in persistent/significant disability/incapacity
- Is otherwise considered medically significant by the investigator.

Expected adverse events:

In this study the following events are potentially expected:

**ESWL:** bleeding on passing urine, pain, urinary tract infection, bruising of abdomen/loin skin, stone fragments stuck between kidney and bladder, infection, kidney damage and persistence of stones.

**Ureteroscopy:** burning or bleeding on passing urine, temporary insertion of bladder catheter, insertion of stent and further procedure to remove it, pain, inability to retrieve stone, movement of stone into kidney, kidney damage or infection, failure to pass the telescope, recurrence of stones, damage to ureter, scarring of ureter.

## 4.2 Recording and reporting AEs and SAEs

### *Assessing and recording AEs and SAEs*

Non-serious events will not be collected or reported. Planned hospital visits for conditions other than those associated with the ureteric stone will not be collected or reported. Hospital visits (planned or unplanned) associated with further interventions to facilitate ureteric stone clearance will be recorded as an outcome measure, but will not be reported as serious adverse events.

Within TISU, 'relatedness' is defined as an event that occurs as a result of a procedure required by the protocol, whether or not this procedure is the specific intervention under investigation and whether or not it would have been administered outside the study as normal care.

Any SAEs related to the participants' ureteric stone treatment that are not further interventions to facilitate stone clearance (eg if a participant is admitted to hospital for treatment of infection) will be recorded on the serious adverse event form. In addition all deaths for any cause (related or otherwise) will be recorded on the serious adverse event form.

### *Reporting responsibilities of the CI*

When an SAE form is uploaded onto the trial website, the Trial Manager will be automatically notified. If, in the opinion of the local PI and the CI, the event is confirmed as being *serious* and *related* and *unexpected*, the CI or Trial Manager will notify the sponsor within 24 hours of receiving the SAE notification. The sponsor will provide an assessment of the SAE. The CI (or Trial Manager) will report any related and unexpected SAEs to the main REC and the DMC within 15 days of the CI becoming aware of it. All related SAEs will be summarised and reported to the Ethics Committee, the Funder and the Trial Steering Committee in their regular progress reports.

## 5 OUTCOME MEASURES

### 5.1 Primary outcome measure

The study has a primary clinical and a primary economic outcome reflecting the multidimensional nature of the possible effects the intervention may have.

**Clinical** Clearance of ureteric stones operationally defined as "no further intervention required to facilitate stone clearance" up to 6 months from randomisation.

**Economic** Incremental cost per quality adjusted life years (QALYs) gained at 6 months from randomisation. QALYs are based on the responses to the EQ-5D.

### 5.2 Secondary outcome measures

**Patient-reported** -measured at pre and 1 week post intervention, 8 weeks and 6 months post randomisation

Severity of pain as measured by the Numeric Rating scale (NRS), generic health profile as measured by the SF-12, (8 weeks and 6 months only), health status as measured by the EQ5D, use of analgesia, acceptability of received procedure (8 weeks and 6 months only)

**Clinical** Further interventions received, complications up to 6 months post randomisation

**Economic** NHS primary and secondary care use and costs up to 6 months, patient costs; incremental cost per surgical interventions averted.

## 6. DATA COLLECTION AND PROCESSING

### 6.1. Measuring outcomes

#### Measurement and timing of outcome assessment (see Table 1: Source and timing of measures)

Outcome data will be collected throughout the trial from consent until six months following randomisation. See Table 1 for detail.

### 6.2. Schedule of data collection

**Table 1: Source and timing of measures**

| Outcome measures                          | Source   | Timing      |                     |                |                               |          |
|-------------------------------------------|----------|-------------|---------------------|----------------|-------------------------------|----------|
|                                           |          | Recruitment | Intervention
Pre | 1 week
post | Post randomisation
8 weeks | 6 months |
| Additional interventions received         | CRF & PQ |             |                     |                | ✓                             | ✓        |
| Pain (NRS)                                | PQ       | ✓           | ✓                   | ✓              | ✓                             |          |
| Health status EQ5D                        | PQ       | ✓           | ✓                   | ✓              | ✓                             | ✓        |
| Health profile SF-12                      | PQ       | ✓           |                     |                | ✓                             | ✓        |
| Use of analgesics                         | PQ       | ✓           | ✓                   | ✓              | ✓                             |          |
| Complications                             | CRF      |             |                     |                | ✓                             | ✓        |
| NHS primary and secondary health care use | PQ & CRF |             |                     |                |                               | ✓        |
| Participant costs                         | PQ       |             |                     |                |                               | ✓        |

### 6.3 Data Processing

Research Nurses will enter locally-collected data in the centres. Staff in the Study Office will work closely with local Research Nurses to ensure that the data are as complete and accurate as possible. Follow up questionnaires to participants will be sent from and returned to the Study Office in Aberdeen. Extensive range and consistency checks will further enhance the quality of the data.

## 7. SAMPLE SIZE, PROPOSED RECRUITMENT RATE AND MILESTONES

### 7.1 Sample size

The original sample size calculations reflect that the TISU trial is a non-inferiority design. Published literature  suggests the proportion stone free without further intervention up to six months in the ureteroscopy arm will be about 0.75 (P1) and in the ESWL arm about 0.65 (P2). The margin of inferiority deemed acceptable is 0.20 so that  $P2 - P1 > -0.20$ . The sample size was estimated using simulations, designed for this purpose, run in Stata. The power of a non-inferiority trial can be considered as the probability that the lower bound of the estimated confidence interval (CI) around the difference between trial proportions

excludes the margin of non-inferiority. Simulating 1000s of trials of fixed sizes with the parameters P1 and P2 as above indicates that a trial of 450 per arm is required for the lower bound of the estimated 95% CI to exclude -20% with 90% power. Adjustment for potential 10% drop-out inflates the trial to 1000 in total. A trial of this size would have above 90% power to test superiority on secondary outcomes of an effect size of 1/4 of a standard deviation.

Following poor recruitment and interim data analysis of 267 participants the sample size was amended from 1000 downwards to 750. The amendment has been ratified by the trial oversight committees and the sponsor and the funder. Recruitment projections showed us that the original sample size of 1000 was unachievable in a realistic timeframe despite measures implemented to improve recruitment. We agreed with the funder an extension of 18 months to reach a revised sample size of 750. Our original sample size of 1000 included a 15% uplift from 850 to perform the primary analysis under a suitably defined Per Protocol analysis. A Per Protocol analysis, in the special context of a non-inferiority design is often seen as the more conservative approach than the conventional intention to treat analysis.

This Per Protocol analysis would have excluded any participants that crossed over from their randomly allocated treatment to the other, and would have excluded any participant whose stone cleared before their randomly allocated treatment was initiated. However, the view of the HTA Board, which has since been confirmed by the TISU iDMC, is that the intention to treat (ITT) approach should take primacy over this Per Protocol approach, to better reflect that the purpose of this pragmatic effectiveness trial is to compare the policy of initiating one or other of these treatment options, and not to focus on the actual comparative performance of the treatment options themselves. The Per Protocol approach will still be used as a supporting analysis. This is also a rare context in which there is no missing outcome data, since we are sure that we will have identified any further interventions to facilitate stone clearance in the 6 months post operatively - hence we can say with certainty for each individual randomised whether the original operation cleared the stone.

Based on the 267 participants with mature outcome data as of the 16 February 2016, the iDMC observed that all the assumptions behind the power calculation remain plausible. Given that we are now committed to the ITT approach rather than the Per Protocol approach (and under, the original design of assuming the proportion stone free in ESWL arm would be 65%, and 75% in the ureteroscopy arm) the achievable sample size of 750 will give 85% power. If we recruit 750, under the assumption of 15% crossover and stone clearance, prior to initiation of the randomly allocated intervention, then the per protocol analysis of 638 subjects will still retain ~80% power under the same assumptions as above.

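### Section 7.1 claims that no primary outcome data can be missing, against the protocol's own withdrawal rules and earlier 10% drop-out allowance, so the 85% power assumes essentially complete ascertainment of all 750

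*Protocol*

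**What the plan says.** The primary outcome (section 5.1) is that no further intervention is needed to clear the stone within six months of randomisation. Failure therefore requires a recorded event, and success is the absence of one.

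Section 7.1, in justifying intention to treat as the primary analysis and the cut from 1000 to 750, states: "This is also a rare context in which there is no missing outcome data". The reason given is that all further interventions in the six months after the operation will have been found, so that the result is known for certain for each person randomised. It then states that "the achievable sample size of 750 will give 85% power". The success rates behind that figure are unchanged from the first calculation: "the proportion stone free in ESWL arm would be 65%, and 75% in the ureteroscopy arm". The only reduction applied to the 750 is 15% for the per-protocol set, leaving 638 with about 80% power.

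Other parts of the protocol bear on this:

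- Section 3.3.5: when consent is withdrawn, questionnaires stop, "however permission will be sought for the research team to continue to collect outcome data from their health care records". Everyone else is followed for all outcomes as far as that can be done.
- Section 3.3.6, on notification by GPs: "GPs are asked to contact the Study Office if one of the participants moves, becomes too ill to continue or dies".
- Section 3.3.4 and Table 1: further interventions come from case report forms completed at the recruiting centre and from participant questionnaires.
- Section 7.1, first paragraphs: "Adjustment for potential 10% drop-out inflates the trial to 1000 in total", and later "Our original sample size of 1000 included a 15% uplift from 850", the latter described as serving the per-protocol analysis.

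**The concern.** A claim that nobody can have a missing outcome cannot stand beside a withdrawal rule under which the records may be closed to the trial. Nor does it agree with the 10% drop-out that the same section first allowed. The claim carries weight: it is the only reason given that could explain why the 750 has no loss allowance, and it leaves no place for a participant whose status is unknown.

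Two different consequences follow, depending on how such participants are handled. If they are left out, the trial has less power than stated. If they are kept and the lack of a recorded intervention is read as clearance, both arms move towards 100% success and the difference between them shrinks. In a non-inferiority trial that error favours the conclusion being tested.

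A smaller mismatch adds to this. Section 7.1 rests its certainty on six months after the operation, whereas the outcome and the case report forms run to six months from randomisation.

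**Working it through.** **Inputs.** From section 7.1: ureteroscopy 0.75, ESWL 0.65, margin 0.20, lower bound of a two-sided 95% interval (one-sided 0.025), 750 randomised, 638 per protocol, original drop-out 10%. Assumed: equal allocation (375 per arm), consistent with the protocol's own 450 per arm.

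**Formula.** With n per arm, SE = √[(0.75×0.25 + 0.65×0.35)/n] = √(0.415/n), and power = Φ((0.20 − 0.10)/SE − 1.96).

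**1. The plan's own figures.**
- n = 375: SE = 0.03327, power = Φ(3.006 − 1.96) = 85.2%. A simulation of 400,000 trials gives 85.4%. The stated 85% reproduces.
- n = 319 (638 in all): 79.2%. The stated figure of about 80% reproduces.
- The smallest n for 85% is 373 per arm, or 746, so the slack is 750 − 746 = 4 participants.

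**2. Participants without an ascertained outcome are excluded.**

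| Loss | Analysed | ITT power |
|---|---|---|
| 0% | 750 | 85.2% |
| 2% | 735 | 84.5% |
| 5% | 712.5 | 83.4% |
| 6% | 705 | 83.0% |
| 10% | 675 | 81.4% |

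For the per-protocol set, 638 × 0.9 ≈ 574, about 287 per arm, gives about 75%. Holding 85% with 10% loss would take 746/0.9 ≈ 829 randomised.

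**3. No recorded intervention is counted as success.** Let a fraction m of each arm be untraced, with the same true rates as the rest. The apparent rate is p(1 − m) + m, and n stays at 375.

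Under the design rates with m = 10%, 0.75 becomes 0.775 and 0.65 becomes 0.685. The difference is −0.09 and nominal power rises to 92.7%.

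With the true difference at the margin (0.75 v 0.55), the chance of wrongly declaring non-inferiority is Φ((0.20 − apparent deficit)/SE − 1.96):

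| m | Apparent rates | Difference | One-sided error |
|---|---|---|---|
| 0% | 0.750 v 0.550 | −0.200 | 2.5% |
| 2% | 0.755 v 0.559 | −0.196 | 3.3% |
| 5% | 0.7625 v 0.5725 | −0.190 | 4.8% |
| 10% | 0.775 v 0.595 | −0.180 | 8.7% |

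If the 10% were untraced in the ESWL arm only, the apparent rates would be 0.75 v 0.595 and the error about 26%. Of these rates only the 10% appears in the protocol, as a planning figure for drop-out. The others are illustrative.

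**4. The two accounts of 1000.** 900/(1 − 0.10) = 1000 and 850/(1 − 0.15) = 1000. Each is arithmetically right, but they start from different evaluable numbers and allow for different losses. Power at 450 per arm is 90.9% and at 425 per arm 89.3%, so both are close to the stated 90%.

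**The case against.** The protocol has a good answer to much of this. The outcome is record-based, and the tracing routes are several: the health record (protocol summary), site case report forms at eight weeks and six months, participant questionnaires with up to two reminders, and the GP. The GP notice in section 3.3.6 is itself a tracing route, since the Study Office may also approach the GP. Only formal withdrawal of consent ends questionnaire follow-up, and permission to use records is sought even then. The monitoring committee saw 267 participants with mature outcomes and found the power assumptions plausible. Missingness on this outcome may therefore be well below 10%, and leaving out the 10% was a reasoned choice rather than an oversight. An untraced participant is also misclassified only if a further intervention actually took place.

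All of that stands, and it limits the size of the problem. It does not turn a low rate into a certain zero, which is what section 7.1 asserts and what section 3.3.5 contradicts.

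Three stronger readings are tempting, and the document does not support them. A reader might infer that untraced participants will be scored stone-free. Section 7.1 implies this but states no such rule, and the statistical analysis plan, which may set the handling, is not at hand. A reader might also add the power loss to the inflated error, but these are alternatives: scoring unknowns as success keeps all 750 and raises nominal power. Finally, a reader might say that 85% fails with any loss at all. Losses up to about 6% stay within two or so points of it.

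**Conclusion.** The concern holds in a limited form. The claim of no missing primary outcome data is wrong as stated, because it conflicts with the withdrawal provisions and with the drop-out allowance used earlier in the same section. The revised 85% is correct arithmetic for essentially complete ascertainment of all 750, and the text does not present that as an assumption.

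The power consequence is modest: at the protocol's original 10%, ITT power stays above 80%, and the larger shortfall falls on the per-protocol analysis, which section 7.1 calls supporting. The possible effect on the error rate matters more, because it favours non-inferiority. It depends on an unwritten scoring rule, on illustrative rates of untraced participants, and on those participants resembling the rest. Severity is moderate. The two accounts of the 1000 are a minor inconsistency about a superseded target and do not affect the 750 or its reproduced power.

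**What to change.** 1. In section 7.1, delete the no-missing-data claim, or qualify it to say that missingness is expected to be low because the outcome is taken from records.
2. Count success only where a case report form or record review confirms follow-up to six months from randomisation with no further intervention, and use that time origin in section 7.1 as well.
3. Treat participants without that confirmation as missing, and provide one sensitivity analysis unfavourable to ESWL. The imputation details can sit in the statistical analysis plan.
4. Restate power as 85% with complete data and about 81% with 10% loss (per protocol about 79% and 75%).
5. Reconcile the two accounts of the original 1000, as a minor correction.

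The cost is wording, one sensitivity analysis and a slightly less favourable stated power. No extra patients are needed.

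### Section 7.1 uses 65% v 75% for both the ITT power (85%) and the per-protocol power (~80%) and changes only n, although the excluded 15% are selected by outcome and treatment received

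*Protocol*

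**What the plan says.** All of this is in Protocol section 7.1, except where noted.

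- **Design inputs.** The success proportions, taken from published literature, are about 0.75 for ureteroscopy and 0.65 for ESWL. "The margin of inferiority deemed acceptable is 0.20". The criterion is "for the lower bound of the estimated 95% CI to exclude -20% with 90% power".
- **Original basis.** The target of 1000 "included a 15% uplift from 850 to perform the primary analysis under a suitably defined Per Protocol analysis".
- **Per-protocol set.** It leaves out participants who crossed to the other treatment, and participants whose stone cleared before the allocated treatment began.
- **Revised basis.** ITT is now primary and per protocol is supporting. At 65% and 75%, "the achievable sample size of 750 will give 85% power".
- **Per-protocol power.** "under the assumption of 15% crossover and stone clearance, prior to initiation of the randomly allocated intervention", the protocol states that "the per protocol analysis of 638 subjects will still retain ~80% power under the same assumptions as above".
- **Outcome.** Section 5.1 defines success as needing no further intervention to help the stone clear, up to six months from randomisation.
- **Analysis.** Section 8 provides for both analyses, as is recommended for non-inferiority trials, and compares their confidence intervals with the margin.

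**The concern.** The step from 85% to ~80% treats the excluded 15% as if they had been removed at random. The protocol's own definition says otherwise. A stone that clears before treatment is ordinarily a success under the section 5.1 outcome in whichever arm it occurs, so removing such participants lowers the success rate in those who remain. A crossover received the other arm's treatment, so crossovers in both directions pull the ITT rates together. In general, then, the ITT and per-protocol populations will not share the same two rates or the same 10-point difference. The protocol does not say which population 65/75 describes.

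The stake is interpretation. Section 7.1 notes that per protocol is often seen as the more conservative analysis in a non-inferiority trial, and its ~80% suggests that this check stays nearly as well powered as the primary analysis. If the true figure is nearer one half, a per-protocol interval that crosses -0.20 would be unsurprising even when the ITT assumptions are right. Readers could take it as evidence against ESWL.

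**Working it through.** **Inputs (section 7.1).** Ureteroscopy 0.75; ESWL 0.65; margin 0.20; lower limit of a two-sided 95% CI; 750 randomised; 15% excluded; 638 analysed. I assume 1:1 allocation, so 375 and 319 per arm (750 x 0.85 = 637.5).

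**1. Reproduce the stated figures.** With U for ureteroscopy and E for ESWL:

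power = Phi[(0.20 - (pU - pE)) / SE - 1.96], SE = sqrt[pU(1 - pU)/nU + pE(1 - pE)/nE]

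- 375 per arm: SE = sqrt(0.415/375) = 0.0333; 0.10/SE = 3.006; power = Phi(1.046) = 85.2%.
- 319 per arm: SE = sqrt(0.415/319) = 0.0361; 0.10/SE = 2.772; power = Phi(0.813) = 79.2%.

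Simulating 200,000 trials at each size gives 85.4% and 79.3%. Both stated powers are correct for their n at 65/75. Only n changed between them.

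**2. Link the two populations.** Let c be the share cleared before treatment (ITT success) and x the share crossing over, the same in both arms, with c + x = 0.15. Crossovers succeed at the rate of the treatment received. With pE and pU the per-protocol rates:

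- ITT(E) = c + x pU + (1 - c - x) pE
- ITT(U) = c + x pE + (1 - c - x) pU

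Subtracting: ITT difference = (1 - c - 2x)(pU - pE). Adding: ITT(E) + ITT(U) = 2c + (1 - c)(pU + pE).

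**3. If 65/75 are ITT rates.** Then pU - pE = 0.10/(1 - c - 2x) and pU + pE = (1.40 - 2c)/(1 - c).

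| Make-up of the 15% | Per-protocol ESWL v ureteroscopy | Difference (points) | Power, 319 per arm |
|---|---|---|---|
| All cleared | 58.8% v 70.6% | 11.8 | 59% |
| Half and half | 61.1% v 74.0% | 12.9 | 49% |
| All crossed over | 62.9% v 77.1% | 14.3 | 36% |

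**4. If 65/75 are per-protocol rates.** Per-protocol power stays at 79%. The ITT figures become:

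| Make-up of the 15% | ITT ESWL v ureteroscopy | Difference (points) | Power, 375 per arm |
|---|---|---|---|
| All cleared | 70.3% v 78.8% | 8.5 | 95% |
| Half and half | 68.4% v 76.1% | 7.8 | 96% |
| All crossed over | 66.5% v 73.5% | 7.0 | 97% |

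**5. When both stated powers can be right.** The excluded participants must average 65% success in the ESWL arm and 75% in the ureteroscopy arm. With 7.5% cleared and 7.5% crossed over in each arm, crossovers must succeed at 30% and 50%:

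- ESWL arm: 0.075 + 0.075 x 0.30 = 0.0975 = 0.15 x 0.65
- Ureteroscopy arm: 0.075 + 0.075 x 0.50 = 0.1125 = 0.15 x 0.75

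If more than 9.75% of the ESWL arm clears, with 15% excluded there, no crossover success rate is low enough.

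**6. Sensitivity, with ITT held at 65/75.**

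*Unequal exclusions*, clearance only, 15% overall. Each per-protocol rate is (ITT rate - c)/(1 - c), using that arm's c.

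| Cleared, ESWL / ureteroscopy | Per-protocol rates | n per arm | Power |
|---|---|---|---|
| 20% / 10% | 56.3% v 72.2% | 300 / 338 | 19% |
| 12.5% / 17.5% | 60.0% v 69.7% | 328 / 309 | 78% |
| 10% / 20% | 61.1% v 68.8% | 338 / 300 | 91% |

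*Crossovers scored as ITT failures*, equal exclusions. Each per-protocol rate is (ITT rate - c)/0.85.

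- Half and half: 67.6% v 79.4%, power 66%.
- All crossed over: 76.5% v 88.2%, power 79%.
- All cleared: unchanged at 59%.

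**The case against.** A reader might infer that 65/75 is impossible in both populations, so that one stated power must be wrong. The documents do not support that: step 5 gives a combination in which both hold. What can be said is that the coincidence needs an assumption the protocol does not make or defend.

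A reader might also take 36-59% as the range for the true per-protocol power. It is not. Section 7.1 gives only a pooled 15%, with no split by arm or reason, and does not say how a crossover is scored. Modest imbalance by arm brings power back to 78%, close to the stated figure, and larger imbalance moves it well outside 36-59% in either direction. The lower figures also depend on crossovers taking the received treatment's success rate.

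The choice of population is open as well. The rates come from the literature and were first attached to a target that section 7.1 says was sized for a per-protocol primary analysis. On that reading ~80% is right and the 85% for ITT is understated.

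Finally, a reader might conclude that the ITT test is anti-conservative because it can declare non-inferiority when the difference among those treated as allocated reaches 20 points. That mixes two questions. Section 7.1 deliberately makes the comparison of initial treatment policies primary. When the policy difference really is inside the margin, declaring non-inferiority is not an error of that analysis.

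All four objections stand against the stronger readings. None supplies the missing justification for carrying 65/75 unchanged from one population to the other.

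**Conclusion.** The point holds as an unsupported power statement. Each figure is computed correctly for its n, but the pair rests on the unstated assumption that the excluded 15% succeed on average at 65% and 75%.

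With equal exclusions in both arms, clearances counted as successes, crossovers succeeding at the received treatment's rate and a Wald 95% interval, one of the two figures is off. Either per-protocol power is about 59%, 49% or 36% rather than ~80%, or ITT power is about 95-97% rather than 85%. These values show the size of the problem under those assumptions and do not bound it.

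The reach is limited. On either reading, this point does not show the primary ITT analysis to be less well powered than stated, and per protocol is a supporting analysis. What is affected is how a per-protocol interval crossing -0.20 should be read beside the ITT result.

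**What to change.** In section 7.1:

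1. State whether 65% and 75% describe the ITT or the per-protocol population.
2. Split the 15% into pre-treatment clearance and crossover, and by arm. The pooled data on the 267 participants with mature outcomes could inform the split by reason. Pooled data cannot show the split by arm, so that should be a stated assumption with a range.
3. Say how a crossover is scored on the primary outcome.
4. Derive the other population's rates and replace the power that no longer follows, giving the result with its range. That is the ~80% if 65/75 are ITT rates, or the 85% if they are per-protocol rates. The illustrative figures above should not be copied in as they stand.

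The cost is a short recalculation and a few sentences. No extra participants, no new data collection and no change to the primary analysis are needed. One stated figure may become less favourable.
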